## **5 Methods**

### **5.1 Study parameters/endpoints**

The study included key patient characteristics, such as age, gender, height, weight, and New York Heart Association (NYHA) class. Echocardiographic parameters included left ventricular ejection fraction (LVEF), mitral valve aetiology, MR severity, left atrial volume index (LAVi), effective regurgitant orifice area (EROA), regurgitant volume, and systolic pulmonary artery pressure (sPAP). Follow-up data, including all-cause mortality and heart failure hospitalisations, are collected during annual follow-up and verified through medical records, with dates recorded. The registry additionally captures mitral valve interventions and other cardiac procedures that may influence outcomes. HRQoL is assessed at baseline and annually using the 36-Item Short Form Survey (SF-36). Additional variables, including detailed echocardiographic measurements (e.g., vena contracta, PISA radius, LVEDD, LVESD) and comprehensive follow-up variables (e.g., cardiac interventions), are presented in the appendix.

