### **5.3 Study procedures**

The database does not require any changes to the participants' usual care, and they will not undergo any procedures other than echocardiographic evaluation and follow-up. Follow-up will take place through regular outpatient visits at the referring hospital. Participating patients will be asked to complete an annual SF-36 questionnaire, with follow-up occurring once yearly for five years. Completing the SF-36 questionnaire will take approximately 15 minutes. Additionally, data from patient records will be collected for five years.

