## 7 Statistical analyses

### 7.1 Baseline, primary, secondary outcomes

Analysis will begin with descriptive statistics to summarise baseline characteristics. Categorical variables will be presented as counts and percentages and compared using the Chi-square test. Ordinal variables will be reported as frequencies and compared using ordinal or non-parametric tests. Continuous variables will be presented as means ( $\pm$  standard deviations) or medians (interquartile ranges), depending on the distribution, and compared using the independent t-test for normally distributed data or the Mann–Whitney U test for non-normally distributed data.

Time-to-event outcomes, including all-cause mortality and time-to-first heart failure hospitalisation, will be analysed using Kaplan–Meier estimates and compared using the log-rank test. Associations between baseline characteristics and clinical outcomes will be evaluated using multivariable Cox proportional hazards regression models, with results presented as hazard ratios (HRs) and 95% confidence intervals (CIs). A minimum of 10 events per variable will be considered to ensure statistical robustness.

Longitudinal changes in echocardiographic parameters and HRQoL will be analysed using mixed-effects models to account for repeated measurements within patients. MR severity will be demonstrated as an ordinal outcome, while continuous echocardiographic measures and HRQoL outcomes will be analysed using linear mixed-effects models. Treatment success will be evaluated using responder-based analyses based on annual follow-up assessments, and predictors of treatment success will be analysed using multivariable logistic regression models, with results presented as odds ratios (ORs) and 95% CIs. Analyses will be stratified by MR aetiology and, where appropriate, by management strategy (conservative, catheter-based, or surgical). Missing data will not be imputed; primary analyses will be conducted using all available data, with sensitivity analyses performed in complete-case cohorts. Statistical significance will be set as a two-sided  $p$ -value  $< 0.05$ .

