### **8.2 Recruitment and consent**

The SMILE registry operates under a no-objection system. Patients are eligible for inclusion when moderate-severe MR is observed on a cardiac echocardiogram. These eligible patients are informed about the study through communication via post or telephone, and they are provided with detailed information regarding the purpose and scope of the registry. Patients are explicitly allowed to object to the use of their data. If no objection is raised, their data will be included in the registry. This method ensures compliance with ethical principles while facilitating a comprehensive and unbiased collection of data necessary to evaluate and improve the quality of care for MR patients.

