|  | Cardiac interventions         | Categorical | Transcatheter Edge-to-Edge Repair, Mitral Valve Replacement, Mitral Valve Repair, Tendyne Transcatheter Mitral Valve Replacement system, Neochord Transapical Artificial Chordae Repair system, Carillon Mitral Contour System (percutaneous indirect annuloplasty), Percutaneous Coronary Intervention, Coronary Artery Bypass Grafting, Aortic Valve Replacement, Permanent Pacemaker implantation, Implantable Cardioverter-Defibrillator implantation, Pulmonary Vein Isolation, None |

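### Section 7.1 lets survival analyses be stratified by a management strategy that is undefined and not recorded at baseline; grouping by later treatment would make mortality favour intervention with no true effect

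*Protocol*

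**What the plan says.** The relevant statements are all in the protocol.

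- **Time-to-event method (7.1):** "Time-to-event outcomes, including all-cause mortality and time-to-first heart failure hospitalisation, will be analysed using Kaplan–Meier estimates and compared using the log-rank test".
- **Regression (7.1):** "Associations between baseline characteristics and clinical outcomes will be evaluated using multivariable Cox proportional hazards regression models".
- **Stratification (7.1, the next paragraph):** "Analyses will be stratified by MR aetiology and, where appropriate, by management strategy (conservative, catheter-based, or surgical". No start of follow-up for the strategy strata, no landmark and no time-dependent treatment variable is given.
- **Entry (8.2):** "Patients are eligible for inclusion when moderate-severe MR is observed on a cardiac echocardiogram". Follow-up is annual for five years (5.3).
- **Capture of treatment (5.1):** "The registry additionally captures mitral valve interventions and other cardiac procedures that may influence outcomes". This comes directly after the sentence on follow-up data.
- **Variable list (13 Appendix):** the baseline characteristics contain no strategy or planned-treatment item. Procedures ("Transcatheter Edge-to-Edge Repair, Mitral Valve Replacement, Mitral Valve Repair" and others) form one categorical item in the one-year follow-up block, with no date row beside it.
- **Treatment success (11.4):** one group is patients who undergo mitral valve intervention. The other is patients managed conservatively, for whom a later mitral intervention rules out success.

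**The concern.** Patients enter at the qualifying echocardiogram, but with the listed variables a patient can be called catheter-based or surgical only once the procedure has happened. To reach either group the patient must first survive the wait. Deaths during the wait fall to the conservative group, and the survived waiting time is credited to the intervention group. This is immortal-time bias, and for mortality it pushes towards intervention.

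All-cause mortality is a co-primary endpoint (2.1), and the introduction names better treatment strategies among the registry's aims. A survival gap created only by the grouping rule would bear directly on that aim.

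**Working it through.** The protocol states no event rate, waiting time, sample size or effect size, so there is no planned figure to reproduce. Every rate below is an assumption. From the documents come the five-year horizon, entry at the echocardiogram, and the two-sided 0.05 level (7.1). In every scenario intervention has no effect, so the true ratio is 1.00.

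**1. Closed-form check of the mechanism.** Assume constant death rate d = 0.10 per year, constant intervention rate w = 0.10 per year, every patient a candidate, and T = 5 years. Let s = d + w = 0.20. Per patient enrolled:

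- Dies untreated: (d/s)(1 − e^(−sT)) = 0.5 × (1 − 0.3679) = 0.3161.
- Alive and untreated at 5 years: e^(−sT) = 0.3679.
- Ever treated: 1 − 0.3161 − 0.3679 = 0.3161 (equal to the first line because d = w).
- Treated and alive at 5 years: e^(−dT)(1 − e^(−wT)) = 0.6065 × 0.3935 = 0.2387.
- Deaths among the treated: 0.3161 − 0.2387 = 0.0774.

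Five-year survival is 0.2387/0.3161 = 76% in the ever-treated and 0.3679/(0.3161 + 0.3679) = 54% in the never-treated.

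Person-years from baseline:

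- All patients: (1 − e^(−dT))/d = 3.935.
- Never-treated: d[1 − e^(−sT)(1 + sT)]/s² + T·e^(−sT) = 0.661 + 1.839 = 2.500.
- Ever-treated: 3.935 − 2.500 = 1.435.

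Naive rate ratio = (0.0774/1.435)/(0.3161/2.500) = 0.0540/0.1264 = **0.43**.

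Now count time before the procedure as untreated. Untreated time is (1 − e^(−sT))/s = 3.161 and treated time is 3.935 − 3.161 = 0.774. The ratio is (0.0774/0.774)/(0.3161/3.161) = 0.100/0.100 = **1.00**. The whole apparent benefit is misallocated waiting time.

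**2. A setting with lasting conservative management.** Assume 40% are destined for intervention, exponential waits, five-year survival of 80, 65 or 50%, and a 30% five-year risk of heart failure hospitalisation. Cox models were fitted to 40,000 simulated patients per scenario. Hazard ratios for death, ranges over the three survival levels:

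| Median wait (years) | Ever vs never treated, from baseline | Time-dependent treatment | One-year landmark |
|---|---|---|---|
| 0.25 | 0.86 to 0.88 | 0.99 to 1.01 | 0.99 to 1.02 |
| 0.5 | 0.73 to 0.76 | 0.96 to 1.00 | 0.94 to 0.99 |
| 1 | 0.61 to 0.64 | 0.98 to 1.02 | 0.96 to 1.02 |
| 2 | 0.53 | 0.97 to 0.99 | 0.98 to 1.04 |

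The wait drives the size; the survival level barely matters.

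**3. False-positive rate for death.** With 400 patients (an assumed number), 65% five-year survival and 300 runs per wait, ever-versus-never grouping was significant at 0.05 in 11%, 32% and 71% of runs for waits of 0.25, 0.5 and 1 year. Almost all of these were in the protective direction. Time-dependent and landmark analyses gave about 3 to 6%.

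**4. First heart failure hospitalisation, same grouping.**

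- Hospitalisation unrelated to intervention and death: hazard ratio 0.99 to 1.03, so no protective bias.
- Hospitalisation triples the death hazard: 0.95.
- Hospitalisation raises the intervention rate fivefold: 8.8, or 5.6 if it also triples the death hazard. Intervention then looks harmful. Time-dependent treatment gives 1.01 and 0.97.

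**5. What the timing fix leaves behind.** In the last scenario (fivefold trigger, tripled death hazard) the time-dependent hazard ratio for death is 1.38 and the landmark gives 1.11, although intervention does nothing. That is confounding by indication.

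**The case against.** The case on the other side is substantial, and several stronger readings that a reader might infer are not supported.

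- **That the protocol commits to this survival comparison.** The strategy stratification is conditional, and its sentence closes the paragraph on longitudinal measures and treatment success, not the one on survival. The Cox models are for baseline characteristics. This stands. But the sentence speaks of analyses without restriction, gives no criterion for when strategy applies, and does not exclude the survival curves.
- **That strategy must mean treatment ever received.** Section 11.4 makes a later intervention a failure of conservative management, which would be an empty condition if conservative meant never treated. An initial-strategy label fits that sentence better, and under it immortal time is small or absent. Yet the same section defines the other group by undergoing intervention, and no listed baseline field could support an initial label. A patient treated in year 2 fits both descriptions.
- **That the bias always favours intervention.** This is true for death only. Hospitalisation can precede and prompt a procedure, so the waiting time is not immortal for that endpoint.
- **That the ratio is 0.43 or lower.** If every patient is a candidate, death rates of 0.06 to 0.14 and intervention rates of 0.05 to 0.50 per year give about 0.18 to 0.47. At 0.50 per year, 1 − e^(−2.5) = 92% of five-year survivors are treated, so the conservative group is largely early deaths. This is one assumed extreme.
- **That the listed data could not correct the bias.** The appendix also lists death and hospitalisation only as yes or no, while sections 5.1 and 11.1 say their dates are recorded. A missing date row does not show that intervention dates are not held; the protocol simply does not say that they are.
- **That this belongs in the SAP.** The detail of a landmark does. But the protocol itself names the strata, the log-rank method and the variables, and followed literally with the listed data they lead to the biased grouping.

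Finally, section 2.2 asks to describe management strategies, not to compare their effectiveness. Stratified results mislead only when the strata are compared.

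**Conclusion.** The concern holds as a conditional one. Section 7.1 permits a between-strategy survival comparison on an undefined label, and the variables listed lead to forming that label from later treatment. If that is done from baseline, the null hazard ratio for death is about 0.87 to 0.53 for median waits of 0.25 to 2 years with 40% destined for intervention, and lower if all patients are candidates. The direction for death follows from the grouping rule. The size rests on assumed rates, above all the wait, which the protocol does not give. For heart failure hospitalisation no single direction can be claimed. The documents do not show that the sponsor has chosen the biased analysis, nor that it could not be corrected. A correct treatment of time removes the immortal-time bias but does not make the strategy groups comparable.

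**What to change.** In section 7.1:

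1. Define management strategy and its time zero. If an initial plan is meant, say so and record it at baseline.
2. Limit Kaplan–Meier and log-rank analyses stratified from baseline to factors known then, such as aetiology.
3. For any between-strategy comparison of death or heart failure hospitalisation, enter catheter-based and surgical intervention as time-dependent covariates, with person-time before the procedure counted as conservative. Alternatively, use a prespecified landmark among patients event-free at that time.
4. Label strategy results as descriptive, because confounding by indication remains.

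In section 5.1 and the appendix, state that the date of each mitral intervention is recorded.

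The cost is a few sentences and at most one date field, plus a baseline field if an initial plan is meant. The downside is small: a landmark drops early events, and time-dependent results are harder to plot than ordinary Kaplan–Meier curves.

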### **5.4 Schedule of assessment**

No additional procedures are planned. All assessments will follow the standard care protocol.

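### Section 7.1 rules out imputation and leaves complete-case cohorts as the only missing-data sensitivity analysis, which cannot test the missing-data assumption of the Cox, logistic or mixed models

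*Protocol*

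**What the plan says.** Protocol section 7.1 sets one rule for all analyses: "Missing data will not be imputed; primary analyses will be conducted using all available data, with sensitivity analyses performed in complete-case cohorts". It does not define the complete-case cohort and states no missing-data assumption. The protocol names no other missing-data analysis.

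The same section specifies the models to which the rule applies:

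- Clinical outcomes: "Associations between baseline characteristics and clinical outcomes will be evaluated using multivariable Cox proportional hazards regression models".
- Treatment success: "predictors of treatment success will be analysed using multivariable logistic regression models".
- Repeated measures: "Longitudinal changes in echocardiographic parameters and HRQoL will be analysed using mixed-effects models to account for repeated measurements within patients".

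It also sets a guide for model size: "A minimum of 10 events per variable will be considered to ensure statistical robustness".

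On the source of the data, section 5.4 says: "No additional procedures are planned. All assessments will follow the standard care protocol". Section 5.3 adds: "Participating patients will be asked to complete an annual SF-36 questionnaire, with follow-up occurring once yearly for five years". Section 5.5 allows withdrawal at any time and keeps the data collected until then. Death within five years is a co-primary endpoint (section 2.1). The covariate associations and the predictors of treatment success are secondary objectives (section 2.2).

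**The concern.** Incomplete records are to be expected. The covariates come from routine care, the appendix lists many echocardiographic measurements, and follow-up runs for five years in a population in which death is an endpoint.

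A sensitivity analysis is useful if it relaxes or varies the assumption behind the primary analysis. The one fixed here does neither. For the Cox and logistic models it either reproduces the primary fit or moves to a more selected subset. For the mixed models it replaces a weaker assumption with a stronger one. Agreement could then be reported as robustness when it shows nothing of the kind, and disagreement could cast doubt on a primary result that is sound.

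The ban has a second cost. Every patient dropped for one missing covariate takes any death or hospitalisation out of that model, so fewer predictors fit within the protocol's own events-per-variable guide, particularly once analyses are stratified by aetiology and management strategy.

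**Working it through.** The protocol gives no sample size, event count or missingness rate, so there is no stated figure to reproduce. All rates below are assumptions.

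**1. Cox and logistic models: which patients enter.** A simulated data set had 1000 patients and models with 4 covariates, each missing independently at 5%, 10% or 20%. Fitted to all available data without imputation, the models used 819, 649 and 406 patients. Fitted to patients complete on the model's variables, they used the same 819, 649 and 406, and the largest coefficient difference was 0.0. This follows from the definition: without imputation, a patient with a missing covariate contributes nothing to the fit.

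If complete-case instead means complete on every annual visit, the cohort differs. Read literally, a patient who dies before the year-5 visit cannot belong to it. For mortality and heart failure hospitalisation that is selection on the outcome, or on something close to it.

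**2. Share of patients kept.** With *k* covariates each missing with probability *m*:

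- independent missingness: share kept = (1 − m)^k
- fully coinciding missingness: share kept = 1 − m

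| k = 10 | m = 5% | m = 10% |
|---|---|---|
| Independent | 0.95^10 = 0.599 | 0.90^10 = 0.349 |
| Fully coinciding | 0.95 | 0.90 |

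Ten variables at 10 events each need 10 × 10 = 100 events among the patients kept. If events are lost in proportion to patients, the registry must hold 100/0.599 ≈ 167 events (5%) or 100/0.349 ≈ 287 (10%) under independence. If missingness coincides, it must hold 100/0.95 ≈ 105 or 100/0.90 ≈ 111.

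**3. Mixed models: all observed visits against completers.** The simulation had 600 patients, a baseline and five annual visits, a random intercept and slope, a true slope of −2.0 per year, a true year-5 mean of 50, monotone dropout and 40 replicates. A few fits gave convergence warnings.

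| Dropout | Slope, all visits | Slope, completers | Year-5 mean, all visits | Year-5 mean, completers | Completers |
|---|---|---|---|---|---|
| Completely at random (MCAR) | −2.03 | −2.04 | 49.8 | 49.5 | 54% |
| MAR | −1.96 | −1.53 | 50.2 | 60.9 | 45% |
| MNAR | −1.15 | −1.15 | 54.4 | 62.7 | 43% |

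Under MAR the two slopes disagree although the primary is nearly unbiased. Under MNAR they agree although each is off by 2.0 − 1.15 = 0.85 per year. The year-5 means differ by about 60.9 − 50.2 = 10.7 under MAR, where the primary is right, and by 62.7 − 54.4 = 8.3 under MNAR, where it is wrong. Comparing completers with the primary therefore does not tell a sound primary from a biased one.

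**The case against.** The strongest reply is that the point rests on an undefined term. Section 7.1 does not say on what a case must be complete. Exact duplication needs completeness on the model's variables; selection on survival needs completeness on all visits. One definition cannot give both for the same model, and the zero difference in step 1 only restates the first definition. This stands, so duplication cannot be claimed as what the protocol says. It does not rescue the rule, because neither definition yields a check of the missing-data assumption.

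Several stronger readings are tempting and are not supported:

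- *That the completer analysis is always more biased.* Under MCAR neither analysis was materially biased, and under MNAR the slopes were equally biased. The clear contrast is a MAR result.
- *That listwise deletion biases the Cox and logistic coefficients.* It costs precision. It remains consistent if missingness depends only on covariates in the model, and biases when missingness also depends on the outcome given those covariates. The protocol gives no evidence on this.
- *That the co-primary results are compromised.* Kaplan-Meier and log-rank analyses need no covariates beyond a grouping variable.
- *That a large loss is to be expected.* Inclusion requires an echocardiogram, age and gender should be nearly complete, and values from one examination tend to be missing together. The events guide is also softly worded and recruitment has no cap, so it is not shown to bind.
- *That the SF-36 is sent by post.* Sections 5.7 and 8.2 mention post or telephone only for informing patients about the registry.

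It can also be said that imputation models belong in a statistical analysis plan. Their detail does. But the protocol states a prohibition, and a plan that imputed would contradict it.

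**Conclusion.** The concern holds in a limited form. The protocol bans imputation outright, and its only missing-data sensitivity analysis cannot test the assumption that matters. In the Cox and logistic models it either repeats the primary or uses a subset selected on survival and follow-up. In the mixed models it needs a stronger assumption than the primary, is biased under MAR where the primary is not, and cannot reveal MNAR bias. Using all observed visits in the mixed models is sound and should stay.

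The effect falls on the secondary objectives. The loss of patients cannot be stated from the protocol: for 10 covariates at 5-10% missing each, anything from 35% to 95% may be kept, depending on the rate and on how far missing values coincide. The sizes of bias in the mixed-model simulation depend on the assumed dropout; the direction of the MAR comparison is the transferable part. The rule should be changed, since a better one is available at little cost.

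**What to change.** In section 7.1, replace the missing-data sentence with provisions that:

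1. Remove the blanket ban on imputation and state the missing-data assumption for each type of model.
2. For the Cox and logistic models, use multiple imputation of missing baseline covariates. The imputation model should contain the outcome (for Cox, the event indicator and the cumulative hazard), centre and the other covariates. Report the complete-case fit as the comparator, defined as complete on that model's variables.
3. For echocardiographic measures and quality of life, keep likelihood-based mixed models on all observed visits. Replace the completer sensitivity analysis with a delta-adjusted (MNAR) one, without imputing values after death.

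The change costs wording and some programming and needs no new data. Its downside is that the imputation models and the range of delta must be specified and checked; that detail can sit in the statistical analysis plan.
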